### Endpoints

The primary endpoint of the study will be a change in cfPWV between baseline and 40 weeks. Secondary endpoints are: (i) change in brachial BP; (ii) change in eGFR; (iii) change in uACR; (iv) change in pulse waveform characteristics; (v) incidence of hyperkalaemia; (vi) incidence of renal dysfunction (increment of creatinine ≥30% or reduction of eGFR ≥25% from baseline); (vii) incidence of other adverse events.

### Sample size calculation and planned statistical analysis

In our recent study of the effect of spironolactone, the Chronic Renal Impairment in Birmingham II (CRIB II) study, the standard deviation of the change in cfPWV was 1.0 m/s in the active treatment group and 0.9 m/s in the control group. Hence, 100 subjects in each arm will provide 90% power with an *α* value of 0.05 to demonstrate a difference in change of cfPWV of 0.5 m/s between the active treatment and control groups. We aim to recruit 240 patients to account for an approximate drop-out rate of 20%, which will result in at least 200 patients completing this randomized control trial, with 100 patients in each arm (inactive placebo versus spironolactone).

The difference in the primary outcome between experimental conditions will be assessed using generalized mixed models. Repeated measures within a subject will be characterized as *R* side residual over-dispersion parameters, accounting for baseline values. Frequency differences will be tested using Fisher’s exact test. A prespecified multivariable analysis will examine the influence of change in systolic BP and other relevant factors on changes in the primary endpoint. Outcomes will be analyzed using intention-to-treat analysis. A *P* value of less than 0.05 will be considered statistically significant.

Data entry, coding, security, storage, access and quality assurance will be managed according to PC-CRTU policy [54]. Study investigators will have access to the final trial dataset.

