Aldosterone is a mineralocorticoid that is a key effector of the RAAS. *In vitro*, it is implicated in numerous CV effects, including endothelial dysfunction, transmural arterial inflammation, myocardial and vascular hypertrophy and fibrosis independent of BP control [33-36]. In human beings, a high aldosterone level is associated with higher left ventricular mass, increased arterial stiffness, endothelial dysfunction and insulin resistance [37]. The importance of increased arterial stiffness in CKD is evidenced by the strong independent association of this parameter with mortality in patients with CKD [38,39]. Treatment with mineralocorticoid receptor antagonists (MRAs) has been proven to confer a powerful prognostic benefit in patients with heart failure by the RALES and EPHESUS studies [40,41] and was confirmed in a meta-analysis [42]. In patients with CKD, MRAs are associated with significant decreases in proteinuria [43,44]. Additionally, in a randomized, double-blinded, placebo-controlled trial of 112 patients with stage 2 or 3 CKD in the secondary care setting, Edwards *et al.* demonstrated that the addition of spironolactone 25 mg once daily (a nonselective MRA) to background ACEI or ARB treatment safely and effectively reduced left ventricular mass (-14 ± 13 g versus +3 ± 11 g, *P* < 0.01) and decreased arterial stiffness, as measured by carotid-femoral pulse wave velocity (cfPWV: -0.8 ± 1.0 m/s versus -0.1 ± 0.9 m/s, *P* < 0.01), compared with placebo [45-47]. A trial to examine whether these desirable intermediate endpoints changes can be translated into long-term gains in terms of reduced CV morbidity and mortality in large CKD cohort is clearly warranted.

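### The stated 90% power does not follow from its own inputs: 100 completers per arm gives about 96%, an error in the safe direction

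*Protocol article*

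**What the plan says.** In the protocol article, the section on sample size calculation and planned statistical analysis reports, from the earlier spironolactone trial, that "the standard deviation of the change in cfPWV was 1.0 m/s in the active treatment group and 0.9 m/s in the control group". The next sentence presents the power as a consequence of these SDs: "100 subjects in each arm will provide 90% power", at an alpha of 0.05, "to demonstrate a difference in change of cfPWV of 0.5 m/s between the active treatment and control groups".

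The 100 per arm are completers. The same section says "We aim to recruit 240 patients to account for an approximate drop-out rate of 20"%, which is meant to leave "at least 200 patients completing this randomized control trial, with 100 patients in each arm (inactive placebo versus spironolactone").

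The Background section gives the same SDs for the same earlier trial: after a minus sign, the cfPWV changes read "0.8 ± 1.0 m/s versus -0.1 ± 0.9 m/s". The two places agree, so a misprinted SD is unlikely.

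**The concern.** The section prints every input for a standard comparison of two means and then a result that those inputs do not produce. Power is a headline planning figure, and a reader who repeats the calculation gets a clearly different answer. The reader cannot tell whether the power was miscalculated or whether an assumption lies behind it that is not printed.

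What is at stake is whether the planning statement can be reproduced. The adequacy of the trial is not in question, because the discrepancy means more power than claimed.

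**Working it through.** **Inputs** (sample size section unless noted)
- SD of change: 1.0 m/s active, 0.9 m/s control (the Background section agrees)
- Difference to detect: 0.5 m/s
- Alpha: 0.05. Sidedness is not stated; two-sided is assumed and one-sided is also tried
- Completers: 100 per arm
- Stated power: 90%

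**Step 1. Power at 100 per arm**
- Standard error of the difference: sqrt((1.0² + 0.9²)/100) = sqrt(1.81/100) = 0.1345 m/s
- Standardised difference: 0.5/0.1345 = 3.72
- Normal approximation: Φ(3.72 − 1.96) = 96.0%
- Noncentral t: 95.9%; Welch test: 95.9%

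The stated 90% is not reproduced.

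**Step 2. Completers needed for 90%**
- Normal approximation: n = (1.0² + 0.9²) × (1.960 + 1.282)²/0.5² = 76.1, so 77 per arm
- Noncentral t: 77 per arm gives 89.98% and 78 gives 90.35%, so 78 per arm

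The stated 100 is 22 per arm more than the inputs require.

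**Step 3. Variants that might rescue the figure**

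| Variant | Power at 100 per arm | n per arm for 90% |
|---|---|---|
| SDs 1.0/0.9, two-sided (t) | 95.9% | 78 |
| SD 1.0 in both arms, two-sided (t) | 94.0% | 86 |
| SD 0.9 in both arms, two-sided (normal) | 97.5% | 69 |
| SDs 1.0/0.9, one-sided (normal) | 98.1% | 63 |

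None comes within 2 points of 90%. A one-sided alpha moves further away.

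**Step 4. What would give 90% at 100 per arm**
- A common SD of about 1.085 m/s (t-test; 1.09 by the normal approximation), or
- a difference of about 0.44 m/s with SDs 1.0/0.9, or
- SD 1.0 in both arms with a two-sided alpha of 0.025 (90.2%, normal approximation).

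The section states none of these. A separate route leads to the 100 itself: 78/(1 − 0.20) = 97.5, close to 100. On that route the 100 would already contain the dropout allowance, whereas the text treats it as completers and inflates again to 240.

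**Step 5. Power with the stated dropout**
- 240 × (1 − 0.20) = 192, or 96 per arm
- Standardised difference: 0.5/sqrt(1.81/96) = 3.64
- Noncentral t: 95.2%; with SD 1.0 in both arms, 93.1%

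The shortfall from 200 to 192 is a separate point. It does not alter the conclusion here.

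**The case against.** The strongest case on the other side is that nothing turns on the error. The planned number exceeds what the stated inputs need, so 90% read as a floor is met, even at 96 per arm. No endpoint, analysis or recruitment target changes. This stands, and it makes the point a reporting correction. It does not make the sentence right: the text gives 90% as the power that follows from the SDs, without saying that it is a minimum.

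A second objection is that the article condenses a full protocol, which may record a variance allowance. That is possible, and it is a reason to ask which assumption was used. But the point is not an omission. The article prints a complete calculation whose result does not follow from its inputs.

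Three stronger readings are tempting and are not supported:
- **That the later definitive trial would inherit a wrong relation between SD and sample size.** The Discussion says that trial would study cardiovascular morbidity and mortality, so it would presumably be sized on event rates and not on the SD of change in cfPWV. The SDs are printed consistently, so anyone reusing them can recompute n.
- **That the 0.5 m/s difference is mis-stated.** Nothing in the text suggests this.
- **That a larger SD was allowed because primary-care patients are more varied.** The Background calls them older and less well characterised, but nowhere links this to the variability of change in cfPWV. That rationale should not be supplied on the sponsor's behalf.

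**Conclusion.** The point holds as an arithmetic and reporting error. With the printed SDs, difference and alpha, 100 completers per arm gives about 96% power, not 90%, and 90% needs about 78 per arm. With the larger SD in both arms the figures are 94.0% and 86 per arm, so the mismatch does not depend on how the two SDs are combined.

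The result assumes a two-sided test and a simple comparison of mean changes; a one-sided test widens the gap. The cause cannot be determined from the document: a larger SD, a stricter alpha or a dropout allowance counted twice would each come close to the printed figures, and none is stated.

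A reader might infer that the trial is inadequately sized. The reverse is true: at both 100 and 96 per arm, power is above the stated value.

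**What to change.** Restate the power as about 96% with 100 completers per arm (about 95% with 96 per arm) for a difference of 0.5 m/s, with SDs of 1.0 and 0.9 m/s and two-sided alpha 0.05.

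If the sponsor did reach 90% through another assumption, state that assumption instead. Examples are a common SD of about 1.085 m/s, or a dropout allowance already inside the 100. Only the sponsor can say whether one was used.

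The cost is one sentence. The sample size, recruitment and conduct stay as they are.

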## Design

This is a multicentre, prospective, randomized, placebo-controlled, double-blinded pilot trial in patients with stage 3 CKD. Patients registered in participating primary care practices within South Birmingham, England will be screened with a view to recruiting 240 eligible participants. Potential participants will be identified by searching computerized primary care clinical records for patients with biochemical evidence of stage 3 CKD (defined as an eGFR of 30 to 59 ml/min per 1.73 m^2^). The GFR will be estimated by the four-variable MDRD formula with serum creatinine recalibrated to be traceable to an isotope-derived mass spectroscopy method [49]. Potentially eligible patients will receive a patient information sheet (Additional file 1) and be invited to attend a screening visit at their own general practice, where the study will be explained further. Written consent will be obtained by the research team prior to enrolment into the study (Additional file 2). Following the screening visit, all recruited eligible, consenting participants will be randomized to receive either placebo or spironolactone 25 mg once daily orally for 40 weeks. Participants will be followed up during the duration of treatment and for 6 weeks after discontinuation of trial medication (wash-out period). The total study duration is 46 weeks. The cfPWV will be measured using a Vicorder (Skidmore, Bristol, UK) system [50] at baseline, week 40 and week 46 to detect any change in arterial stiffness. Outcomes will be analyzed using an intention-to-treat analysis.

Ethical approval has been received from the National Research Ethics Service West Midlands Coventry and Warwickshire (Reference No 12/WM/0168) and clinical trial authorization has been granted by the Medicine and Healthcare Products Regulatory Agency (MHRA) (Reference No 21761/0274/001-0001). The research team will seek further approval from the National Research Ethics Service and the MHRA for any protocol modifications. The sponsor, investigators, trial steering committee (TSC), data management committee (DMC), coordinating centre, recruiting sites, all members of the study team and all trial participants will be informed of the modifications.

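### At the stated 20% drop-out, 240 recruits leave about 192 completers (96 per arm), not 200 or more: a minor arithmetic error that leaves the stated power intact

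*Protocol article*

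**What the plan says.** All the figures are in the protocol article, section Sample size calculation and planned statistical analysis.

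- Recruitment and retention: "We aim to recruit 240 patients to account for an approximate drop-out rate of 20%, which will result in at least 200 patients completing". The sentence then splits the 200 equally, 100 to each group.
- Power: "100 subjects in each arm will provide 90% power with an *α* value of 0.05". The target is a between-group difference of 0.5 m/s in how much cfPWV changes.
- Variability, taken from the investigators' earlier spironolactone study: "the standard deviation of the change in cfPWV was 1.0 m/s in the active treatment group and 0.9 m/s in the control group".

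The Abstract and the Design section repeat the target of 240 but give no drop-out rate and no number of completers.

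**The concern.** One sentence links three numbers: 240 recruited, about 20% lost, and a floor of 200 completing. Any two of them fix the third, and the third as printed does not match. The floor is also the number to which the power statement is tied, 100 per arm.

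Two things could be at stake. One is power, if the shortfall were large enough to bring it below the stated 90%. The other is how retention is read. This is a pilot whose first listed objective (Table 1) concerns recruitment and feasibility, and it is meant to inform a definitive trial. As the text stands, a trial that recruited 240 and lost exactly the planned share would fall short of its own completer figure. If the same step were used to size the definitive trial, it would again recruit too few for its stated loss rate.

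**Working it through.** **Inputs**, all from the sample size section: N = 240 recruited; loss d = 0.20; 200 completers, 100 per arm, so equal allocation; difference 0.5 m/s; SDs 1.0 and 0.9 m/s; alpha 0.05. The section does not say whether alpha is one-sided or two-sided, so two-sided is assumed.

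**Step 1. Reproduce the printed target.**
- Adding 20% to the completers: 200 x 1.20 = 240. This matches the printed target exactly.
- Allowing for a 20% loss among recruits: 200 / (1 - 0.20) = 250. This does not match.

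The article does not show which step was taken. The first is consistent with its figure, and that is as much as can be said.

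**Step 2. Completers from 240 at 20% loss.**
- N x (1 - d) = 240 x 0.80 = 192, or 96 per arm.
- Shortfall: 200 - 192 = 8 patients (4 per arm), which is 8/200 = 4% of the stated number.

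**Step 3. The loss at which 240 does leave 200.**
- 1 - 200/240 = 40/240 = 16.7%.

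| Loss | Completers from 240 |
|---|---|
| 15% | 204 |
| 16.7% | 200 |
| 18% | 196.8 |
| 20% | 192 |

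**Step 4. What 96 per arm does to power.**
- Common SD: sqrt((1.0² + 0.9²)/2) = sqrt(0.905) = 0.951 m/s.
- Standard error at 96 per arm: 0.951 x sqrt(2/96) = 0.137. The ratio 0.5/0.137 is about 3.64, and 3.64 - 1.96 = 1.68, which gives about 95% power.

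Power of an unadjusted two-sample t-test (noncentral t):

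| Per arm | SD 0.951 | SD 1.0 in both arms |
|---|---|---|
| 100 | 95.9% | 94.0% |
| 96 | 95.2% | 93.1% |

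Four fewer per arm cost less than one percentage point.

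**Step 5. Numbers needed for 90% power.** The normal approximation gives 77 per arm (SD 0.951) or 85 per arm (SD 1.0). Correctly inflated for 20% loss, these need 2 x 77 / 0.80 = 192.5, so 193 recruits, or 2 x 85 / 0.80 = 212.5, so 213 recruits. Both are below 240.

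**The case against.** The strongest defence is that the drop-out rate is called approximate, and the figures agree at 16.7%, only 3.3 points away. This narrows the gap but does not close it. The sentence promises a floor, the floor holds only up to 16.7% loss, and the rate it names is above that limit.

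A second defence is that the analysis is by intention to treat with a mixed model, and that withdrawn participants are asked to attend a final visit that includes the stiffness measurement (Withdrawal criteria). Completers are then not strictly the number analysed. That is fair as far as it goes. But the visit is voluntary, it falls within 7 days of stopping trial medication and so is not a week-40 measurement, and the protocol's own sentence counts completers.

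A third objection concerns importance, and it stands. No stopping rule or success criterion in the article depends on reaching 200 completers, and the stated power is still exceeded on the printed inputs.

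Three stronger readings are tempting, and the document supports none of them:

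- That the trial is underpowered or must recruit 250. Steps 4 and 5 show otherwise on the printed SDs.
- That 200 is known to have been multiplied by 1.2. The match is exact, but the step is not shown, so this remains an inference.
- That the Design section contains a second error. It says only that patients will be "screened with a view to recruiting 240 eligible participants", which conflicts with nothing by itself.

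**Conclusion.** The completer figure is wrong as written. At the stated loss rate the expected number is about 192 (96 per arm), 8 fewer than printed, and nothing else in the article reconciles it. The error is minor and changes no feature of the design.

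The statement about power rests on the printed SDs and difference, a two-sided alpha (assumed) and an unadjusted two-sample t-test. The planned analysis is a mixed model that accounts for baseline, so the power figures are a guide and not an exact account of that model.

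One qualification applies. On the printed SDs, 100 per arm gives about 96% power, so the stated 90% is conservative. A reader who took 90% at 100 per arm as exact would be assuming an SD of about 1.09 m/s (0.5 x sqrt(100/2) / (1.96 + 1.28)). Power at 96 per arm would then be about 89%. The article prints no such SD, and even in that case the loss is about one point.

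**What to change.** Keep the target of 240 and change one sentence, in one of two ways:

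- Correct the completers: with about 20% loss, 240 recruits are expected to leave about 192 completers, 96 per arm.
- Or correct the allowance: 240 recruits leave 200 completers, 100 per arm, provided that loss does not exceed about 16.7%.

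The first is preferable if 20% is the real expectation. It can carry a short note that 96 per arm still exceeds 90% power for 0.5 m/s with SDs of 1.0 and 0.9 m/s and two-sided alpha 0.05. The stated 90% need not be replaced to make this correction. The Abstract and the Design section stay as they are. The cost is one sentence, with no extra patients and no change to the analysis. For the definitive trial, divide the required completers by one minus the expected loss.

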### Trial management

The STOP-CKD study will be coordinated by the PC-CRTU at the University of Birmingham according to the current guidelines for Good Clinical Practice. The chief investigator takes overall responsibility for the conduct of study. Any delegated or devolved responsibility will be documented in a delegation log. An investigators group will meet monthly to provide oversight of the developing trial, with more frequent operational meeting of the chief investigator, trial manager and trial team as required.

A TSC will be appointed and will provide overall supervision for the trial, in particular: trial progress, protocol compliance, patient safety and review of updated information. The TSC will include the trial management group, two lay representatives and an independent chair who has expertise relevant to the study. The TSC will meet every 3 to 6 months, depending on the phase of the study.

An independent DMC for the trial will be responsible for the regular monitoring of trial data. The committee will consist of an independent secondary care clinician, an independent academic general practitioner and an independent statistician. The DMC will assess the progress of the trial and give advice on whether the accumulated data from the trial, together with the results from other relevant trials, justifies the continuing recruitment of further patients. The committee will meet in person or by teleconference prior to the trial commencement and then 3 and 6 months after initiation of the trial. The DMC will make confidential recommendations to the TSC as the decision-making committee for the trial (Additional file 5).

### Monitoring and safety assessments

Monitoring will be performed according to PC-CRTU policy and be conducted centrally and at each local recruitment sites. Any major problems identified during monitoring will be reported to the TSC. All records will be maintained in accordance with local regulations and in a manner that ensures security and confidentiality. All adverse events and severe adverse events will be recorded and followed up for the duration of the study or until resolution. Assessment of adverse events will be performed by the study investigators. All serious adverse events will be graded and reported to the sponsor. Any suspected unexpected serious adverse reactions will be reported to the sponsor, ethics committee and MHRA.

### Substudies

#### Quality control of laboratory tests

The time lapses from blood sampling to analysis of sample in the biochemistry laboratory in the Queen Elizabeth Hospital Birmingham will be recorded. At week 2, two serum separator tube (SST) samples will be obtained from up to 100 participants. One SST from each of the 100 participants will be centrifuged on site (at the recruited general practice) before sending to the biochemistry laboratory at the Queen Elizabeth Hospital Birmingham for potassium analysis. The other parallel SSTs from the same participants will be sent via the routine specimens transport from the general practices to the laboratory. The serum potassium results from each pair of SSTs will be compared to examine the influence of time delay during routine general practice specimens’ transport on serum potassium results.

#### *Qualitative research study to address development and feasibility issues*

A qualitative research study will be embedded in this pilot RCT to explore patients’ and GPs’ attitudes to CKD, research in CKD and use of spironolactone in CKD in the community setting, and to examine potential barriers for research participation as well as barriers to the use of spironolactone in the community. The outcome of this qualitative study will help to indicate how trial procedures might be modified for a future definitive trial and improve our understanding of the factors that might limit the prescription of spironolactone in community settings.

The data sampling technique includes a one-to-one interview and a focus group. Interviews will be performed at the beginning of the study with the aim of involving both patients and GPs who have agreed or declined to participate in the RCT. Focus groups will be organized after participants have completed the RCT. General practitioners and patients will receive patient information sheets on the qualitative study. Informed written consent will be obtained prior to participation in the qualitative research.

A grounded theory approach [55] will be used to guide sampling, data collection and analysis. Purposive sampling will allow for maximum variety of patient and GP characteristics. Up to 30 patients and 30 GPs will be selected for interview. Up to four focus groups will be organized among participating patients and GPs. Patient sampling will ensure representation of views from participants of different age, ethnicity, socio-economic status and sex. General practitioner sampling will ensure representation of different ages of GP, practice locations and practice sizes. Interviewing will continue until data saturation has been achieved. The interviews will be confidential and face-to-face using a topic prompt, which will be refined over the course of the initial interviews [56]. They will be undertaken by a research fellow, supervised by an experienced qualitative researcher. Both the interviews and focus group meetings will be carried out in a place convenient to the interviewees.

All interviews and focus groups will be audio-taped and transcribed verbatim. Transcriptions will be read and checked for accuracy by the researcher and the text entered into a computerized database using the NVivo (QSR International) qualitative software package [57]. Constant comparative analysis [55] will be used to interpret the data. Data collection and analysis will be iterative, with new data being used to confirm or challenge emerging concepts.

